
**Figure 2 figure2:**
[figure not shown]
General study protocol.

### Study Periods

Entry into the study (T0) is the first study period and will take place in agreement with the French Agency for the Safety of Health Products and the local ethics committee. The adolescents’ parents agree to be included and sign the informed consent to enter into the clinical active phase of the study. The ASI results will be assessed, taking into account that an insecurity score on the ASI is a prerequisite for entry into the study. The intermediate study period (1 to 24 months, T1) will involve the inclusion criteria described in Textbox 1. In the third (end) study period (30 months, T2) the AOI parameters and neurophysiological data will be analyzed for the adolescent population. The GPACS analyses will be carried out for dyads included in the study. The results will be valorized.

### Outcomes

#### Primary Outcome

The primary outcome is the evaluation of the changes in adolescent-parent interaction using GPACS in the OT versus PB conditions.

#### Secondary Outcome

The secondary outcome is the evaluation of the changes in oculomotor behavior and neurophysiological responses (ie, modification of EDA and HR [88]) in the OT versus PB conditions.

### Safety Procedure

#### Side Effects

Findings show that IN-OT produces non-detectable subjective changes in recipients, and is not associated with adverse outcomes when delivered in doses of 18 to 40 IUs for short-term use in controlled research settings [89].

#### Withdrawal of Individual Participants

Participants may withdraw from the study at any time for any reason and without any sanction. Researchers, after consulting with the principal investigator and the study coordinator, may also interrupt the treatment program if, in their opinion, continuing this treatment is prejudicial to the patient’s welfare. If a participant withdraws or is withdrawn from the study, follow-up at day 30 will be continued whenever possible.

#### Suspension of the Study

In cases where severe adverse events related to the administration of the treatment are suspected, the study will be interrupted and the researchers and coordinator will decide whether to continue.

#### Reporting of Adverse Events

Any adverse events reported spontaneously by the participant or observed by the researcher or the research team will be recorded on the case report form (CRF) designed for this purpose. The researcher will classify the intensity of said adverse events in accordance with a mild to severe scale, and the periodicity of the event will be classified by following a single occurrence to persistent scale (Textbox 2).

The classification scheme for reporting the intensity and periodicity of adverse events.1. Intensity  a. Mild: some discomfort, but not as such as to interrupt normal daily activity.  b. Moderate: sufficient discomfort to reduce or notably affect normal daily activity.  c. Severe: causing incapacity to work or perform normal daily activities.2. Periodicity  a. Single occurrence: just one event of limited duration.  b. Intermittent: various episodes of an event, each of limited duration.  c. Persistent, unlimited: an event that has persisted over time and is of indefinite duration.

For each adverse event, its relation to the medication taken, in the researcher’s opinion (definitive, probable, possible, improbable, none), as well as any action taken as a result, will be recorded on the data collection form. The occurrence of an adverse event that is fatal, potentially fatal or incapacitating, or that requires or prolongs hospitalization, or that provokes severe congenital anomalies will be recorded as a “severe” adverse event (SAE). All SAEs and unexpected adverse pharmacological reactions, defined as adverse events whose nature or intensity is not in accordance with any expected adverse event, will be reported by the researcher to the study coordinator by telephone, mail or fax as soon as is reasonably possible, but in any case within 24 hours of occurrence.

### Data Analysis

#### Statistical Power, Establishment of Sample Size, and Safety

The calculation of sample size will be based on the average score on the 4 negative dimensions (items) of the GPACS between the group of adolescents who will receive treatment with OT and the group that will receive the PB. No clinical studies have used this scale in an attachment study, so this calculation is based on expert opinion (personal communication from [name], author of the GPACS). We estimate that a difference of 5 points for our main criterion is an interesting minimum clinical difference. Based on the supposition of a difference of 5 points for the OT group, a standard deviation value of 6.2 was calculated. We do not have the standard deviation of the values on our primary endpoint. However, we have the standard deviation of each negative item in the GPACS and summarized data from the original validation study of the GPACS. The variability of the values obtained for each of the 4 negative items were summed and we obtained a variability of 0.03 (SD 0.175). If we consider that the sum represents 3% of the total variability (co-variations to be added), then we arrive at a standard deviation of 6.2, a 90% power and an alpha level of 5% unilateral (superiority of trial against PB); therefore 54 patients should be included. Taking into account 10% of error and non-analyzable data, 60 patients should be included (ie, 30 patients per group). The overall significance level of statistical tests will be at 5%.

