The main objective is to evaluate the effect of IN-OT on the behavior and discourse of insecure adolescents during a disagreement (stressful situation) with one of their parents. This evaluation will be based on the average score on the scales (4 negative and 1 positive) of the Goal-Corrected Partnership in Adolescence Coding System (GPACS) (personal communication from [name], author of the GPACS). Secondary objectives will be to evaluate the effect of IN-OT versus PB on visual exploration strategies for images eliciting attachment-related emotions (ie, distress and comfort). This characterization will be based on the study of eye parameters (ie, total picture fixation time, and average number of fixations per emotion) assessed by a remote eye tracking (ET) device.

We are conducting a randomized, double-blind, placebo-controlled protocol in which insecure adolescent male participants received IN-OT or PB. The protocol was designed to investigate the effects of IN-OT on emotion regulation strategies, by testing whether attachment anxiety and avoidance moderate the effects of IN-OT during a conflict discussion with a parent, and during the visualization of attachment-related pictures.

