### Parent-Adolescent Interaction Assessment

The quality of the parent-adolescent interaction will be assessed with the French version of the GPACS. The development of the GPACS drew on prior literature describing behavioral manifestations of security, insecurity, controlling behavior, and behavioral disorganization among younger children toward their parents in stressful situations. It has already been used in several studies [77-79]. The GPACS coding system includes the rating of each interaction on 10 5-point scales from 1 (not at all) to 5 (very much). There are 2 positive scales (1) “Collaborative Communication” indexing cooperative goal-corrected partnership and parent/adolescent carefulness; and (2) “Caregiving Validation of Adolescent’s Voice” indexing the caregiver’s support for the adolescent. There are 8 negative scales characterizing 3 subtypes of disorganized interaction (ie, punitive, caregiving/role confusion, and disoriented behavior). These 8 scales are (1) parental punitive behavior (eg, angry, critical or mocking comments about the adolescent); (2) adolescent punitive behavior (eg, angry, critical or mocking comments about the parent); (3) adolescent disoriented-distractible behavior (eg, suddenly stopping in midsentence and “freezing” with hand in midair or pausing abruptly in mi-sentence); (4) parental disoriented behavior (eg, the same as adolescent disoriented behavior); (5) adolescent odd, out-of-context or contradictory behaviors, which may seem disjointed, startling, or inexplicable to an observer (eg, using a forced, high-pitched, or childish tone of voice, shifting into unusual, fantasy-based topics); (6) parent odd, out-of-context behavior (eg, using a forced, high-pitched, or childish tone of voice, wandering around the room, stiff, usually shifting away from the topic); (7) adolescent attempts to manage or take care of the parent or modulate the parent’s behavior (eg, offering guidance, defusing tension with over-bright, entertaining behavior); and (8) parental role confusion (eg, asking for advice on topics typically discussed with partner or other adult).

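### The 5-point difference and SD of 6.2 behind the sample size do not fit an average of 1-to-5 scales, and 6.2 does not follow from the figures given for it, so the 90% power is unsupported

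*Protocol article*

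**What the plan says.** All references are to the Protocol article.

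- **Score used for the calculation** (Data Analysis, under the heading on statistical power and sample size; below, the sample-size section). Its opening sentence reads: "The calculation of sample size will be based on the average score on the 4 negative dimensions (items) of the GPACS".
- **Score in the main objective** (Current Study): "This evaluation will be based on the average score on the scales (4 negative and 1 positive"), which is five scales and not four.
- **Scoring** (Parent-Adolescent Interaction Assessment): "the rating of each interaction on 10 5-point scales from 1 (not at all) to 5 (very much"). That section describes two positive and eight negative scales.
- **Difference**: "a difference of 5 points for our main criterion is an interesting minimum clinical difference", attributed to expert opinion.
- **SD**: the sample-size section says the SD of the primary endpoint is not available. It starts from the four negative items, where "we obtained a variability of 0.03 (SD 0.175"), and then assumes that "the sum represents 3% of the total variability (co-variations to be added), then we arrive at a standard deviation of 6.2".
- **Result**: 90% power at one-sided 5% gives 54 patients, raised to 60 (30 per group) for 10% non-analysable data.

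**The concern.** The difference and the SD are larger than the scoring allows for an average of 1-to-5 ratings. The SD also cannot be recovered from the two figures said to produce it. This is the article's only power statement.

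Two readings of the results depend on it. A null result might be taken to exclude a relevant effect with 90% power. An observed difference might be compared with a 5-point minimum that an average of these scales can never reach.

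**Working it through.** **1. The plan's own N.** Inputs from the sample-size section: difference 5, SD 6.2, one-sided 5% (z = 1.645), power 90% (z = 1.282), two equal groups.

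- d = 5/6.2 = 0.806
- n per group = 2(1.645 + 1.282)² / 0.806² = 26.3, so 27 per group and 54 in total
- 54/0.9 = 60

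Both figures reproduce. A t-based calculation gives 28 per group, with power 89.96% at 27, which is the same for practical purposes.

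**2. Do 5 and 6.2 fit the score?**

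| Reading | Range | Largest difference in means | Largest SD, (max − min)/2 |
|---|---|---|---|
| Average of 1-to-5 scales (as written) | 1 to 5 | 4 | 2 (2.02 as a sample SD, n = 60) |
| Sum of 4 scales | 4 to 20 | 16 | 8 |

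On the average, 5 and 6.2 are both out of range. On the sum both are attainable. An SD of 8 needs half the participants at the minimum on all items and half at the maximum. A uniform spread over the 17 integer scores from 4 to 20 has SD √((17² − 1)/12) = 4.9, so 6.2 is implausibly wide.

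**3. Does 6.2 follow from 0.03 and 3%?** Summed item variance: 0.175² = 0.0306.

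- Share taken on variances: 0.0306/0.03 = 1.02, so SD = 1.01.
- Share taken on SDs: 0.175/0.03 = 5.83. Then n per group = 2(2.927)² × (5.83/5)² = 23.3, so 24 per group and 48 in total.
- Working back from 6.2: variance 6.2² = 38.44, and 0.0306/38.44 = 0.08%.

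**4. Can the share be 3%?** For k items, the Cauchy-Schwarz inequality gives Var(sum) ≤ k × (sum of the item variances). The item variances are therefore at least 1/k of the total: 25% for 4 items, 20% for 5, 12.5% for 8, and 10% for all 10 scales. Adding covariances cannot bring the share to 3%. With item variances totalling 0.0306, the SD of a four-item sum is at most √(4 × 0.0306) = 0.35, and that of the average at most 0.35/4 = 0.0875.

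**5. What survives.** Only the standardised effect. With 27 per group, 90% power corresponds to:

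- One-sided 5%: d = 2.927 × √(2/27) = 0.80 (normal), 0.81 (t-based).
- Two-sided 5%: d = (1.960 + 1.282) × √(2/27) = 0.88 (normal), 0.90 (t-based).

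The Statistics section calls d ≥ 0.8 large. For assumed smaller effects (one-sided 5%, 27 per group, normal formula), power is 58% at d = 0.5, 71% at 0.6 and 82% at 0.7.

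**The case against.** **A sum may have been meant.** The section speaks of summing item variabilities and adding covariances, which is how the variance of a total is built, and its average score could mean the group mean of that total. This stands in part. A reader might infer that 5 and 6.2 are impossible outright, but that is true only of the score as worded. On a 4-to-20 sum they are possible, and dividing both by 4 (1.25 and 1.55) leaves d = 0.806 unchanged. The derivation is not rescued, since steps 3 and 4 apply to the sum.

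**Rounding.** On the SD scale, 0.175/6.2 = 2.8%, which rounds to 3%, so 6.2 may have come from an unrounded ratio. That would explain the number without justifying it. The same inequality puts the ratio of √(summed item variances) to the SD of a four-item sum at no less than √(1/4) = 50%.

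**Disclosure.** The article admits that the endpoint SD is unknown and that expert opinion was used. This is fair to note, but it does not make the SD calculation valid.

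**History of the scale.** A reader might also see a contradiction between "No clinical studies have used this scale in an attachment study" and "It has already been used in several studies [77-79"]. The first is limited to clinical use in an attachment study and the second is not, and the documents do not show what kind of studies those were. No contradiction is established, and nothing here depends on one.

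**Conclusion.** The point holds as a fault in the justification of the sample size. The difference and SD do not fit the score as worded, and 6.2 has no valid route from 0.03 and 3% on any reading of the score.

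A reader might infer that 60 is too few or that the true power is below 90%. The documents do not support that. The formula step is right, and no usable SD or difference on the score's own scale is given, so no corrected N can be computed. The plan's variance figures, taken at face value, point to a much smaller SD (about 1, or at most 0.35 for the sum). They more probably signal a misreported input than a real effect of many SDs. Conversely, power would fall to about 58% if the true effect were 0.5 SD, which is an assumed value.

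What can be said is that the design has about 90% power for an effect of about 0.81 SD. The article presents this as a minimum difference of interest, yet its own benchmark calls it large. This rests on 27 analysable participants per group, a roughly normal score and a one-sided 5% test.

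**What to change.** 1. Keep N = 60. The abstract reports that enrolment is complete.
2. Delete the derivation built on 5 points, 6.2 and 3%.
3. First settle the score: sum or average, and which scales enter it. The article gives four negative in the sample-size section, four negative plus one positive in the main objective, and eight negative in the description of the GPACS. If a positive scale is included, state its direction of scoring.
4. Restate the power: 54 analysable participants (27 per group) give about 90% power for a standardised difference of about 0.81 at one-sided 5%, or about 0.90 at two-sided 5%. Say that this is large by the Statistics section's benchmark.
5. Give the minimum important difference on the actual metric, from expert judgement. Take the SD from the validation study's item SDs and inter-item correlations. Do not derive either from the trial's unblinded data. The abstract says analysis began in July 2016, so blinding cannot be assumed.

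The cost is a text correction and one calculation from validation data, with no extra participants. The sponsor holds the item SDs by its own account, but may have to obtain the correlations. The downside is that the detectable effect becomes visibly large.

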#### Statistics

To analyze the quantitative variables, parametric (Student *t*) or nonparametric (Wilcoxon) tests will be used, depending on the distribution of variables. The Shapiro-Wilk test will be used to test the normality of the distributions. Clinical and sociodemographic variables collected at the beginning of the study will be described using the mean (SD) for normally distributed continuous variables, and the median, for non-normally distributed variables. For qualitative variables, the chi-square or Fisher's test will be used to compare proportions between the two groups. Statistical analyses will be conducted and supervised by the Methodology and Biostatistics cell of the Centre of Investigation Clinic (CIC) in Besançon. All data will be analyzed using the SAS application. To estimate the clinical relevance of the findings, Cohen’s effect size (Cohen’s d) will be used for parametric outcomes (large effect ≥ 0.8) and *r* for non-parametric outcomes (large effect ≥.5).

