### Material

#### Oxytocin or Placebo Treatment

Syntocinon (NOVARTIS, Basel, Switzerland) is a synthetic, sterile, clear aqueous solution containing a cyclic nonapeptide, identical to endogenous OT released by the posterior lobe of the pituitary. The excipients are sodium acetate, glacial acetic acid, chlorbutanol, and ethanol. The PB will contain all the ingredients in the Syntocinon spray (saline solution) except for OT. Syntocinon and PB sprays, with identical ampoules and labels, will be prepared and randomly assigned by the research pharmacy at the University Regional Hospital Pharmacy of Besançon. Based on studies of IN-OT in adults [74], age-dependent dosage will be used, with age as a proxy for size and weight. Thus, younger participants (aged 13 to 15) will receive 16 international units (IU, 4 puffs of 4 IU), and older participants (aged 16 to 20) will receive 24 IU (6 puffs of 4 IU).

Inclusion and exclusion criteria for participants.InclusionResults of Attachment Scale Interview (ASI): clinical diagnosis of insecure attachmentMale adolescentEnrolled in high school or collegeNot hospitalizedNo current or past history of neurological or psychiatric illness, including substance abuse or dependenceAged 13 to 20 yearsAble to speak and understand FrenchAccompanied by a parentNormal or adequately corrected visionAffiliation to French social securityNot participating in any other ongoing trialsInformed signed consent of adolescent and both parentsExclusionResults of ASI: clinical diagnosis of secure attachmentFemaleIntellectual deficitSevere neurological symptomsKnown allergies to OT or to preservatives in the nasal spray (in particular, E216, E218 and chlorobutanol hemihydrates)Outside of age rangeNot speaking French (either adolescent or parent)Vision problemsChronic disease (ie, liver failure, kidney failure, or cardiovascular disease)Antihypertensive therapySmokingHeavy alcohol use or drug useParticipation in another ongoing trial

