### Attachment Style Assessment

Attachment will be assessed using a modified ASI, with questions adapted to be applicable to adolescents. This interview elicits the adolescent’s current state of mind regarding the quality of relational experiences with parents and peers. The ASI determines the adolescent’s ability to access and use social support with 3 confidants (ie, parents and peers). This tool assesses relationship quality, social support, and security of attachment style. Several dimensions (ie, mistrust, constraint of closeness, fear of rejection, self-reliance, desire for company, fear of separation, and anger) were coded to determine the attachment profile as either secure or insecure (ie, enmeshed, fearful, angry-dismissive or withdrawn).

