### Procedure

First, a psychologist will evaluate the participant’s diagnostic eligibility. Attachment style will be determined using the ASI [74]. Participants who are classified as insecurely attached will return 1 week later for the OT trial (see Figure 2). Randomization will be centralized and performed after the inclusion of the eligible participants. Participants will be randomly assigned to receive either OT or PB intranasally, with both investigators and participants blind to condition. The randomization code will be kept secret by the pharmacy responsible for dispensing the corresponding medication. To reduce bias, randomization will be performed in blocks, with stratification for confounding factors (eg, age). Experiments will be conducted in a comfortable laboratory during the mid-afternoon hours, in accordance with previous research suggesting stability in the diurnal cycle of plasma OT [84]. Each adolescent will first be asked to choose a topic of disagreement to discuss during the parent-adolescent interaction. Then, 45 minutes before the interaction, the adolescent will be instructed to sit and self-administer 1 puff every 30 seconds, alternating nostrils. The adolescent will take each dose in front of the investigator, to assure correct administration and tolerability. The dosage and timing of the nasal spray administration were chosen based on published research on IN-OT, behavior, and emotions in humans [85], and results on cerebrospinal fluid levels after intranasal vasopressin administration [86]. Dyadic interaction will consist of a 5-minute free conversation and a 10-minute conflict discussion that will both be videotaped. The entire interaction session will be transcribed verbatim, and then coded offline for verbal interaction behavior with the GPACS by coders blind to the study hypotheses. After the dyadic stressful interaction, the adolescent will then be isolated in the ET room for 15 minutes, in order to adapt to experimental conditions. The adolescent will be seated in front of the screen in a comfortable viewing position. After this adaptation phase, the EDA electrodes will be fastened to the second phalanges of the index and middle fingers of the non-dominant hand and 2 ECG electrodes will be placed in a bipolar configuration on interior sides of the participant’s wrists [87]. The RED will perform a 9-point calibration procedure. Once this calibration has been successfully accomplished, the 3 minute baseline responses will be recorded with the BIOPAC system. The participant will be informed that the test is due to start, and that he will freely observe a series of 80 pictures. The neurophysiological monitoring AcqKnowledge 4.3 software will be synchronized with Experiment Center 3.0 (RED SMI) software by event markers representing the beginning of each picture. The participant’s eye movements and neurophysiological recordings (EDA and HR) will begin when the first red dot (approximately 0.95° of visual angle) appears. The task will last for about 15 minutes.

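### The only stated group comparison, a t or Wilcoxon test chosen by Shapiro-Wilk, omits the randomisation strata, leaves the primary estimand to the data and cannot test the stated attachment moderation

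*Protocol article*

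**What the plan says.** - **Analysis.** Protocol article, Statistics: Student t or "nonparametric (Wilcoxon) tests will be used, depending on the distribution of variables". The selection rule is: "The Shapiro-Wilk test will be used to test the normality of the distributions". The effect measure switches on the same basis, between Cohen's d and r. No model, covariate, stratum or interaction term appears.
- **Randomisation.** Procedure: "randomization will be performed in blocks, with stratification for confounding factors (eg, age". No cut-points are given, and age is only an example.
- **Age and dose.** Oxytocin or Placebo Treatment: "younger participants (aged 13 to 15) will receive 16 international units (IU, 4 puffs of 4 IU", while "older participants (aged 16 to 20) will receive 24 IU (6 puffs of 4 IU". The Abstract gives 24 IU without this distinction; those places must be reconciled, which is a separate matter.
- **Aim.** Current Study says the protocol investigates the effects of oxytocin "by testing whether attachment anxiety and avoidance moderate the effects of IN-OT during a conflict discussion with a parent", and also during picture viewing. The same section makes separate predictions for highly anxious and highly avoidant adolescents.
- **Attachment measure.** Attachment Style Assessment: several interview dimensions "were coded to determine the attachment profile as either secure or insecure (ie, enmeshed, fearful, angry-dismissive or withdrawn". No anxiety or avoidance score is named.
- **Sizing.** Statistical Power, Establishment of Sample Size, and Safety: "We estimate that a difference of 5 points for our main criterion is an interesting minimum clinical difference". With SD 6.2, 5% one-sided and 90% power this gives 54, raised to 60. Only the main two-group difference is sized.

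**The concern.** Three parts of the article do not fit the analysis it states.

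1. **Strata.** Stratified randomisation removes between-stratum variation from the treatment contrast. A test that ignores the strata still counts that variation in its standard error, so the standard error is too large if the strata predict the outcome.
2. **Estimand.** Student t concerns a mean difference and Wilcoxon a shift in ranks. With the choice left to a normality test on the trial's own outcomes, neither the primary test nor the quantity it estimates is fixed in advance. If Wilcoxon is chosen, the analysis no longer estimates the quantity behind the sample size.
3. **Moderation.** Moderation is a difference between treatment effects. A two-group test contains no arm-by-attachment term and cannot address it. This matters because the Background cites studies in which oxytocin worked in opposite directions in anxious and avoidant people, and such effects could cancel in a pooled comparison.

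**Working it through.** **Step 1: reproduce the sample size.** Inputs from the sample-size section: difference 5, SD 6.2, one-sided 5%, power 90%.

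n per arm = 2 × (6.2/5)² × (1.645 + 1.282)² ≈ 26.3, rounded up to 27. Total 54, and 54/0.90 = 60. The stated figures reproduce. The exact t calculation gives 89.96% power at 27 per arm. The arithmetic is not at fault; it concerns an unadjusted mean difference.

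**Step 2: cost of omitting the strata.** Let R² be the share of outcome variance explained by the strata. The article gives no figure, so 10 to 30% is an assumption. With balance within strata, the true standard error is the unadjusted one times √(1 − R²), so the one-sided size is about 1 − Φ(1.645/√(1 − R²)):

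- R² = 10%: 1 − Φ(1.734) ≈ 4.1%
- R² = 20%: 1 − Φ(1.839) ≈ 3.3%
- R² = 30%: 1 − Φ(1.966) ≈ 2.5%

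Simulation (27 per arm, two nearly equal strata balanced across arms, 40,000 runs, true difference 5 for power):

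| R² | Size, unadjusted | Size, adjusted | Power, unadjusted | Power, adjusted |
|---|---|---|---|---|
| 0 | 4.9% | 4.8% | 89.9% | 89.9% |
| 10% | 4.1% | 4.9% | 91.0% | 92.5% |
| 20% | 3.2% | 4.8% | 92.2% | 94.8% |
| 30% | 2.4% | 4.8% | 93.7% | 96.9% |

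A second simulation with 28 per arm gave sizes of 4.1, 3.0 and 2.3%, and a power gain of about 1.4 to 3 points. Unadjusted power rises too, because the balance makes the estimate more precise, so the gain from adjustment is modest.

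**Step 3: does the Shapiro-Wilk switch inflate error?** Assuming the check is applied to each arm at 5% (27 per arm, 8,000 runs), the one-sided type I error of the two-stage procedure was 5.1% for normal, 4.7% for exponential and 5.1% for lognormal data. It does not. What remains is that test, estimand and effect measure are settled by the outcome data.

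**Step 4: power for moderation.** Assume two equal attachment subgroups, so four cells of N/4.

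SE of the interaction = 6.2 × √(4/(N/4)).

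- N = 54: 6.2 × √(4/13.5) ≈ 3.37. For an interaction of 5 points, 5/3.37 ≈ 1.48 and two-sided power = Φ(1.48 − 1.96) ≈ 32%.
- N = 60: SE ≈ 3.20, power ≈ 35%.
- For an interaction of 2.5 points, power is 11 to 12%.
- Interaction detectable with 90% two-sided power: 3.37 × (1.960 + 1.282) ≈ 10.9 points at N = 54, and about 10.4 at N = 60.

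**The case against.** The strongest reply has four parts.

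- **The unadjusted test is valid.** It is unbiased and, after stratified randomisation, conservative, and the planned 90% power is met without adjustment. This stands. A reader might infer bias, false positives or a large power loss; the figures above show otherwise. Gains beyond about 3 points would need further predictive covariates, for which the article gives no figures.
- **The strata need not be the dose bands.** A reader might infer that they are 13-15 and 16-20, so that the analysis ignores dose. The article supports only that age is an example of a stratification factor and that age also determines dose.
- **The switch is a stated rule and keeps its error rate.** This also stands. A reader might add that t and Wilcoxon would often disagree on a floor-loaded mean of 1-to-5 ratings. A 5-point difference cannot occur on such a mean, so that simulation does not describe the outcome on which the trial was sized.
- **A condensed article may leave interaction models to a fuller plan.** Moderation is not listed among the primary and secondary outcomes, and Eye-Tracking Measurements says gaze parameters will be related to attachment style, so analyses beyond the Statistics section may be intended. This limits the weight of the point. It does not remove it: the article names a test of moderation as a purpose of the design, and the methods it states cannot perform one. It does not describe separate subgroup tests either, so one should not assume they are planned.

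**Conclusion.** The point holds as a mismatch between design, aim and stated analysis. The randomised comparison itself remains sound.

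- The moderation gap is the most substantial part: a stated aim has no matching method. An added test would have only about 32% two-sided power at N = 54 for an interaction of the full 5 points, so it can only be exploratory. This assumes two equal subgroups and SD 6.2.
- The unfixed estimand is real but does not inflate type I error.
- Omitting the strata costs efficiency only: a one-sided size of about 4.1% down to 2.3% and roughly 1.5 to 3 points of power, for an assumed R² of 10 to 30%. If the strata explain nothing, nothing is lost.

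The article does not show that the attachment interview yields anxiety and avoidance scores, or that trait anxiety is measured before dosing. Neither can be taken as ready for use in a model.

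**What to change.** 1. Prespecify one primary analysis: a linear model of the GPACS score on arm and the actual randomisation strata, with heteroscedasticity-robust or permutation inference, reporting the mean difference with its confidence interval.
2. Drop the Shapiro-Wilk switch and keep a stratified (van Elteren) Wilcoxon test as a sensitivity analysis.
3. Test moderation with arm-by-attachment interaction terms. Define the attachment measures from the interview before unblinding, label the analysis exploratory and report confidence intervals.
4. Add other covariates, such as trait anxiety, only if they are measured before dosing.

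Cost: a few degrees of freedom and minor programming. Fixing a mean-based primary analysis can also give up power if scores are strongly skewed: in the simulated exponential case with a pure shift, the t test had 90% power against 98% for Wilcoxon. That is the price of keeping the estimand on which the trial was sized, and the sensitivity analysis covers it. Timing is the main constraint. The Abstract says analysis began in July 2016, while the Results section puts this in the future. Any change must be fixed before unblinding or be declared post hoc.
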